### Follow-up study procedures and retention

All participants will receive an email with a link to the 3-, 6-, 9-, and 12-month follow-up surveys post randomization. The behavioral surveys will take approximately 30–45 min to complete. They also receive DBS kits at 6- and 12-months.

#### Study Retention

Study participants provide email and text contact information following the formal consent process. Study staff are assigned specific participants with whom to follow up for each study activity, including surveys, DBS home test kits, and randomized treatment or control group assignment. Staff engage participants one-on-one with various text and / or email reminders when participants have not responded to or completed survey invitations, or when they have not returned a DBS kit. Engagement contacts are recorded in each participant record in the study database (REDCap) and follow up is continued for at least three attempts for surveys and at least eight attempts for DBS home test kits. Participants are paid 2–3 business days after completion of each study activity.

***Procedures to maximize engagement in the app***. START Study engagement strategies are outlined in the standard operating procedures (SOP) given to all study staff. Study staff are also trained on participant engagement through one-on-one coaching by the project coordinator.

Study participants are contacted periodically after assignment to the treatment or control group to support their use of the treatment app or the control website. Coordinators check in with treatment group participants within a week after their onboarding visit to ensure the app is working correctly. Additionally, participants will receive a follow up message with resources after the randomization visit with a link to the control website or a link to a video walkthrough of the app. Specifically, study coordinators check in ~ 5 day after enrollment, 7–14 days of inactivity with app, and any participants 30 + days inactive.Additional START User Engagement Procedures have been implemented and added to START Study SOP. Engagement and retention seem to be improving as we apply these new procedures.
2.1.Weekly analysis and reporting on Treatment Group activity: Study staff assigned to engagement reporting reviews daily email from intervention app developer, Radiant, listing study participants assigned to the treatment group who have not opened the intervention (app) for 15 days or more. Using a coordinator account, staff then accesses backend user reports on the app developer’s website to review inactive participants’ check-in data against the dates they opened the app to ensure accuracy. If a discrepancy is noted in these reports, staff reaches out to the app developer to investigate potential tech issues.2.2.Weekly Coordinator Reports and participant outreach: Study staff assigned to engagement reporting reviews all backend user reports on the app developer’s website to track activity of each participant assigned to the Treatment Group in each activity and each module, number of reminders set, and number of videos watched. Each study coordinator receives a full weekly report on all activities of those who have been inactive 15 days or more, with recommendations for outreach suggesting activities the participant has not yet tried or any emerging or recurring patterns that may be useful to the coordinator. Coordinators reach out to participants on this weekly report by text or email to ask if the participant is having any trouble with the app and to suggest news ways to engage. When participants reply with tech issues, such as a forgotten PIN number or new phone, study coordinators help the user resolve the issue and re-engage with the study intervention.2.3.Monthly Engagement Report: The same procedures that are done weekly for Inactive Users are applied to all participants assigned to the Treatment Group once a month, including both active and inactive. Discrepancies are reported to the app developer to identify potential reporting errors or tech issues, and the project coordinator and engagement staff meet with the developer on a regular half-hour weekly video conference call to investigate and address these issues. Coordinators are notified of any issues involving their participants that have been brought to the app developer. Each month, study coordinators are sent a full report on the check-in activity and time in app (times opened) for all their participants, with more detailed notes on individual engagement to personalize their interactions with participants.2.4.Month-to-month comparison for optimization: The activities of all participants in the treatment group during the current month is compared to their cumulative activity reported the previous month, noting any significant changes in engagement for each participant. Coordinators receive specific recommendations for outreach to their study participants in order to optimize engagement, highlighting those whose engagement has notably decreased in the past month.2.5.The project coordinator is notified by direct message with an executive summary of any noteworthy overall trends or discrepancies. The executive summary and any action items are also shared at the next weekly START Team meeting.2.6.Documentation of Engagement: Past engagement reports are stored in study staff shared drive. In addition to being communicated directly, study staff have access to these shared weekly and monthly engagement reports.

## Outcomes

START’s primary outcome of interest is HIV viral load at 6 months through HemaSpot™ DBS collection kit (Table 2). Secondary outcomes of interest measured using validated scales include stimulant use (NM-ASSIST) [70]; ART adherence (Wilson) [77]; ART adherence (VAS) [78] and positive affect (modified DES) [79] (Table 2). Although reduction in sexual transmission risk is important [30], it is not the focus of the intervention; however, since it is intertwined with adherence and drug use, we will assess reduction in potentially amplified transmission risk as a secondary outcome at 6- and 12-month follow-up.

**Table 2 Tab2:** Study measures and administration schedule

		Assessment					
Variable and measure	Items	BL I	BL II	3-month	6-month	9-month	12-month
**Primary Outcome**							
HIV viral load (DBS)	NA	X^a^	—^b^	—	X	—	X
**Secondary Outcomes**							
Stimulant use (NM-ASSIST) [70]	7^c^	X	—	X	X	X	X
ART adherence (Wilson) [77]	3	X	—	X	X	X	X
ART adherence (VAS) [78]	1	X	—	X	X	X	X
Positive affect (modified DES) [79]	26	X	X	X	X	X	X
**Other Variables of Interest**							
Information, motivation, and behavioral skills (LW-IMB-AAQ) [60]	18	X	—	X	X	X	X
ART adherence self-efficacy (HIV-ASES) [80]	17	X	—	X	X	X	X
Engagement in HIV care (Appendix 1)	7	X	—	X	X	X	X
Sexual behavior in aggregate (Appendix 1)	12	X	—	X	X	X	X
Sexual behavior by encounter [81]	19	X	—	—	X	—	X
Depression and anxiety (PHQ-4) [82]	4	X	—	X	X	X	X
Relationship problems (ASI Lite) [83]	9	—	X	—	X	—	X
Social support (MAPSS-SF) [84]	3	—	X	—	X	—	X
Technology use [85]	12	—	X	—	—	—	—
eHealth literacy (eHEALS) [86]	9	—	X	—	—	—	—

*Note* BL = baseline; DBS = dried blood spot; NM-ASSIST = NIDA-modified alcohol, smoking, and substance involvement screening test; ART = antiretroviral therapy; VAS = visual analog scale; DES = differential emotions scale; LW-IMB-AAQ = LifeWindows information–motivation–behavioral skills art adherence questionnaire; HIV-ASES = HIV treatment adherence self-efficacy scale; PHQ-4 = 4-item patient health questionnaire; ASI = addiction severity index; MAPPS-SF = multifactorial assessment of perceived social support, short form; eHEALS = eHealth literacy scale

^a^ X indicates measure is included in assessment

^b^ — indicates measure is not included in assessment

^c^ Items asked for each of ten substances, including methamphetamine and cocaine

### Incentives

Participants will receive incentives electronically to their email through electronic gift card code. Once participants have completed study activities, they will be paid on a bi-weekly basis by the project coordinator. E-gift card incentives will be sent to participants via email where they can redeem the value online for Visa or Mastercard prepaid cards or store-specific gift cards for over 200 different retailers. For DBS kits, the University of Miami will track weekly specimen logs by participant user ID, and the project coordinator will email the participant a gift card code. The consent form will describe the financial incentives for each study time point: $50 for each survey, at baseline, baseline 2, 3-, 6-, 9-, and 12-month follow-up, $35 for HemaSpot™ DBS collection at baseline, $70 for DBS collection at 6- and 12-month follow-up, and $25 for completing onboarding procedures during randomization for a chance to earn up to $500 in incentives.

### Statistical analyses

All study data will be interrogated using both numeric and graphical exploratory data analysis (EDA) methods. The EDA will include but not be limited to frequency tables for all categorical variables (e.g., counts and percentages) and measures of central tendency and variability for continuous variables (e.g., means, medians, standard deviations, IQR, etc.). Range checks will be defined, a priori, for every variable, and odd values will be automatically flagged and reported in nearly real-time reports. This process will allow for the immediate detection of missing data and will the study team to intervene if critical data is missing or implausible. Parametric or non-parametric tests, based on EDA findings (e.g., Chi-square tests, t-tests, Wilcoxon tests), will be used to investigate equality of potential confounders across the START and informational control conditions. If preliminary analyses detect non-trivial imbalance in potential confounders across the intervention and comparison groups that cannot be satisfactorily addressed via covariate adjustment, we will substitute causal inference methods based on the Rubin Causal Model (e.g., propensity score weighting; marginal structural models) [87–91] to obtain population-level effects of the intervention under the assumption of balanced confounders between the groups.

Based on our extensive experience working with this population and documented success with achieving 80% retention at 12 months in the RCT of ARTEMIS, we anticipate up to 20% attrition over the 12-month investigation period. All analysis methods, (i.e., mixed effects models) will be selected to use whatever data is available for each person at each time point. Attrition analyses will compare respondents who complete all measurements to those who do not based on baseline characteristics. Direct maximum likelihood and multiple imputation will be used to address incomplete data because these methods make the relatively mild assumption that missing data arise from a conditionally missing-at-random process [92].

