### Randomization and onboarding

Men who complete the run-in period are asked to attend a separately scheduled onboarding visit with study staff via Zoom where they are randomized using a computer-generated algorithm developed by the study statistician ([name]) for block randomization in randomly permuted blocks of 2, 4, and 6 to guard against subversion. Randomization will be stratified by whether participants are actively seeking formal substance use disorder treatment to achieve balance on this important possible moderator. Treatment and non-treatment seeking men may likely have different intervention needs, which may differentially impact their experience with the START mHealth application and outcomes. Following randomization, participants are provided with a brief overview of the START mHealth application or informational control website that includes referrals to HIV care and substance use disorder treatment resources.

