We plan to test these longitudinal hypotheses and will model outcomes using multilevel random coefficient models (i.e., hierarchical linear modeling; HLM). These models incorporate random intercepts and slopes for each participant based on the participant’s multiple measurements over time [93]. Initial models will follow an intent-to-treat (ITT) approach and compare outcome trajectories for participants in START intervention and informational control condition across time via the group-by-time interaction effect. A priori planned comparisons to address Hypotheses 1a–1b (d) will be performed to test group differences at 6 and 12 months. These planned comparisons will be evaluated at α = 0.05; any subsequent post-hoc comparisons will be adjusted via simulation-based stepdown methods to maintain a nominal Type 1 error rate of 0.05. Multilevel models for continuous outcomes (e.g., positive affect) will be fitted to the data using SAS PROC MIXED [94]. Multilevel models for ordered categorical or binary outcomes (e.g., probability of urine reactive urine toxicology for stimulants and sex risk) will be fitted using SAS PROC GLIMMIX with maximum likelihood estimation via adaptive quadrature with a minimum of 15 integration points [95]. Additional exploratory analyses will investigate moderators of the direct effects of the intervention on ART adherence and viral suppression. Random coefficient models to address hypotheses 1a-1b (d) will be extended to explore moderation by including moderator-by-intervention group and moderator-by-moderator product terms. Secondary analyses will also explore whether the potential mechanisms of change (e.g., reduced stimulant use) mediate the effects of START on ART adherence and viral suppression using the contrast weight-based approach of Kenny for assessing mediation in multilevel models [96]. Multilevel model assumptions (e.g., normal, homoscedastic variances) will be checked; data that do not conform to heteroskedastic-consistent estimators will be substituted for model-based estimators [97].

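### Baseline tests between randomised arms can lead to the planned model being replaced by propensity weighting or a marginal structural model, with no exemption for the primary outcome

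*Protocol article*

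**What the plan says.** Participants are randomised by "block randomization in randomly permuted blocks of 2, 4, and 6", stratified by whether they are seeking substance use treatment (Protocol article, Randomization and onboarding).

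The Statistical analyses section then says that parametric or non-parametric tests "will be used to investigate equality of potential confounders across the START and informational control conditions". The consequence follows at once: "If preliminary analyses detect non-trivial imbalance in potential confounders across the intervention and comparison groups that cannot be satisfactorily addressed via covariate adjustment", then "we will substitute causal inference methods based on the Rubin Causal Model (e.g., propensity score weighting; marginal structural models"), in order "to obtain population-level effects of the intervention under the assumption of balanced confounders between the groups".

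This text stands ahead of Aims 1a and 1b, applies to the analyses generally, and makes no exception for viral suppression at 6 months.

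The default model is given under Aim 1b. "Initial models will follow an intent-to-treat (ITT) approach", and models for binary or ordered outcomes "will be fitted using SAS PROC GLIMMIX with maximum likelihood estimation via adaptive quadrature". Planned comparisons at 6 and 12 months are tested at 0.05. Nothing there says that these models stay primary if the substitution rule comes into play.

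**The concern.** In a randomised comparison the null hypothesis of a baseline equality test is true by design. A small p-value therefore reports a chance event and does not reveal confounding that needs repair. Chance imbalance in a prognostic variable can still matter for precision, but the answer to that is adjustment for covariates chosen beforehand.

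The plan instead lets the baseline table open a route to a different estimator, and its word is substitute: a replacement, not a supporting analysis. Two judgements stand on that route, whether the imbalance is non-trivial and whether adjustment has dealt with it satisfactorily. Both are made after randomised data are in hand, and the second may well involve looking at fitted outcome models.

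Two things are at stake. Which estimator carries the primary conclusion would depend on chance and judgement. The quantity reported could also change, because a random-effects logistic model and a weighted population-level analysis do not estimate the same odds ratio.

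**Working it through.** **Plan's own figures.** The plan gives no figure for how often the rule would operate. Its power figure is not affected by this point and reproduces. The 80% Agresti-Coull limits from 29/45 and 40/42 are 0.7295 (upper, control) and 0.8877 (lower, treated). The two-sided Fisher exact test at 140 per arm then has power 0.906, against the stated 90% or so.

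**Step 1: chance of at least one apparent imbalance.** Table 2 lists 11 measures at the first baseline and 4 further ones at the second, so 11 + 4 = 15. Assume all 15 are tested, independently, at 5%; the article states none of these three things. With k tests the probability is 1 − 0.95^k:

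| Tests k | Probability |
|---|---|
| 4 | 0.185 |
| 8 | 0.337 |
| 12 | 0.460 |
| 15 | 0.537 |
| 20 | 0.642 |

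This covers the first condition only. Substitution also needs adjustment to be judged unsatisfactory, and the documents give no basis for that probability.

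**Step 2: type I error.** Null trials were simulated with 140 per arm, 12 independent normal covariates (2 of them prognostic, log odds ratio 0.5 or 1.0 per standard deviation) and 72% suppression at the covariate mean. There were 20,000 replicates per setting, and arms were compared by linear probability models with robust standard errors. These settings are assumptions. The mechanical rule switched to inverse-propensity weighting whenever any baseline |z| exceeded 1.96, ignoring the plan's second condition and so switching more often than the plan would.

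| Quantity | Log OR 0.5 | Log OR 1.0 |
|---|---|---|
| Any baseline test significant | 0.469 | 0.464 |
| Unadjusted, always | 0.054 | 0.051 |
| Mechanical switch to weighting | 0.050 | 0.044 |
| Most favourable of five analyses once triggered | 0.065 | 0.067 |

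The five analyses were unadjusted, two weighted and two covariate-adjusted. The Monte Carlo standard error is √(0.05 × 0.95 / 20,000) = 0.0015. Automatic switching gave no inflation. Picking by result added about 0.065 − 0.054 = 0.011 to 0.067 − 0.051 = 0.016 over the unadjusted test. A smaller run (10,000 replicates) with a choice of only three analyses gave 0.052 to 0.060.

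**Step 3: shift in the effect measure.** Inputs are the printed planning rates of 72% and 89% (Power and sample size).

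- Population-level odds ratio: (0.89/0.11) / (0.72/0.28) = 8.09 / 2.57 = 3.15.
- Subject-specific odds ratio for a random intercept with standard deviation s: find a and b such that the average of 1/(1 + exp(−(a + s·z))) over standard normal z equals 0.72, and the same expression with b equals 0.89. The odds ratio is exp(b − a).

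| s (assumed) | Subject-specific odds ratio |
|---|---|
| 1 | 3.72 |
| 2 | 5.63 |
| 3 | 9.51 |

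The same two suppression rates thus give an odds ratio anywhere from 3.15 to 9.51, depending on the estimator and on s. Both measures equal 1 under no effect, so this concerns what is reported, not false positives.

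**The case against.** The strongest defence is that substitution is a last resort. It requires non-trivial imbalance and then a failure of covariate adjustment, so it should be rare. The default is identifiable: intent-to-treat multilevel models with planned contrasts at 6 and 12 months. The trigger is covariate imbalance, not the outcome result, and when applied mechanically it left type I error intact in step 2. A covariate list and a threshold for imbalance are matters for an analysis plan that is not shown.

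Most of this stands, and it limits the point. A reader might infer that the primary p-value has lost its 5% level. The documents do not support that, because the simulated error rose only when the analyst picked the most favourable of several results, which the plan does not describe. A reader might also infer that half or more of sound trials would switch estimator. That takes the probability of the first condition for that of both. Nor is it right that no planned estimate can be identified, or that a missing threshold or variable list is itself a fault of the article.

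What the defence does not reach is the stated rule. An analysis plan could define non-trivial and satisfactory, but while that rule stands the primary estimator would still depend on observed imbalance. Describing the multilevel models as initial does not make them final.

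**Conclusion.** The point holds as a rule that is stated and fixed badly. Chance baseline differences and two post-data judgements can replace the primary estimator and move it from a subject-specific to a population-level effect.

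The shift in the odds ratio could be large (3.15 against 3.72, 5.63 or 9.51), but it depends on an assumed random-intercept standard deviation and arises only if the substitution is made. The figure of about 54% for at least one chance imbalance rests on 15 independent tests at an assumed 5% level. Several Table 2 measures concern adherence and are likely to be correlated, and the article does not say that every row would be tested. The effect on type I error ranges from none under a mechanical switch to about 0.065 to 0.067 under favourable picking among five analyses, so the accurate statement is that 5% is not guaranteed. The change should be made; the matter is not grave.

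**What to change.** 1. Describe baseline characteristics by arm, and drop significance tests as a basis for choosing the analysis.
2. Keep one prespecified primary model whatever the baseline table shows. Adjust it for the treatment-seeking stratum, already used in randomisation, and for baseline viral load, for which the run-in requires a viable specimen before randomisation. For each secondary outcome, adjust for its own baseline value.
3. State how baseline enters. If it is a covariate, it should not also be an outcome time point in the same longitudinal model.
4. Replace the substitution sentence with one that labels any propensity weighting or marginal structural model as a sensitivity analysis, and name the effect measure that each analysis estimates.

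The cost is a change of wording. No new data are needed, and the sample size and power statements are unaffected.

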#### Aim 1a

inferential analyses for the primary outcome, viral suppression at six months. Compared to an informational control condition, participants randomized to the START intervention will:

Hypothesis (HYP) 1a: display greater viral suppression at 6 months.

#### Aim 1b

inferential analyses for secondary outcome measures. Compared with an informational control condition, participants randomized to START will:

HYP 1b (a): Display greater viral suppression at 12 months. HYP 1b (b): Have a lower probability of amplified HIV transmission risk. HYP 1b (c): Report greater increases in ART adherence. HYP 1b (d): Report greater increases in theory-based psychological processes such as positive affect, motivation, and self-efficacy.

We plan to test these longitudinal hypotheses and will model outcomes using multilevel random coefficient models (i.e., hierarchical linear modeling; HLM). These models incorporate random intercepts and slopes for each participant based on the participant’s multiple measurements over time [93]. Initial models will follow an intent-to-treat (ITT) approach and compare outcome trajectories for participants in START intervention and informational control condition across time via the group-by-time interaction effect. A priori planned comparisons to address Hypotheses 1a–1b (d) will be performed to test group differences at 6 and 12 months. These planned comparisons will be evaluated at α = 0.05; any subsequent post-hoc comparisons will be adjusted via simulation-based stepdown methods to maintain a nominal Type 1 error rate of 0.05. Multilevel models for continuous outcomes (e.g., positive affect) will be fitted to the data using SAS PROC MIXED [94]. Multilevel models for ordered categorical or binary outcomes (e.g., probability of urine reactive urine toxicology for stimulants and sex risk) will be fitted using SAS PROC GLIMMIX with maximum likelihood estimation via adaptive quadrature with a minimum of 15 integration points [95]. Additional exploratory analyses will investigate moderators of the direct effects of the intervention on ART adherence and viral suppression. Random coefficient models to address hypotheses 1a-1b (d) will be extended to explore moderation by including moderator-by-intervention group and moderator-by-moderator product terms. Secondary analyses will also explore whether the potential mechanisms of change (e.g., reduced stimulant use) mediate the effects of START on ART adherence and viral suppression using the contrast weight-based approach of Kenny for assessing mediation in multilevel models [96]. Multilevel model assumptions (e.g., normal, homoscedastic variances) will be checked; data that do not conform to heteroskedastic-consistent estimators will be substituted for model-based estimators [97].

Secondary analyses will estimate the association between individual features of the START intervention (e.g., number of logins, days self-reported ART, number of modules completed) with ART adherence and VL suppression. These components of the intervention will be treated as predictor variables in regression models with the previously described ART adherence and VL suppression measures the dependent variables. The analytic approach for these secondary analyses will follow those for the primary aims, with regression models (linear or logistic) containing intervention arm as the primary independent variable and adjust for any necessary demographic factors.

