### START mHealth application

Those randomized to receive the app have an account created by the START staff member, are asked to download the app, and are given a START app tutorial during their onboarding visit. Participants are instructed to log into the app and are guided through the Check-Ins, Welcome Videos, My Settings page, Crisis Resources, Skills, Self-Care Check List and other key components (Table 1). Participants are asked to begin the first lesson, Positive Events and Gratitude, and make their way through each lesson on the app as it unlocks. If they have any questions, they are encouraged to reach out to START staff via text or email. Additionally, they are asked to engage with the app several times per week for six months.

**Table 1 Tab1:** START intervention app components and features

Features	Description	Format	Activities
Check-In	Check in on mood, adherence, using drugs/alcohol	Text, graphics	Prompts participant to choose current mood, report if they took their HIV medications yet, and report if they are currently using drugs/alcohol.
Welcome	Introduction to the START app and investigators, self-care, and information about stimulant use and HIV	Text, graphics, video	Choose self-care strategies to implement when stressed
Positive Events and Gratitude	Noticing positive events, developing gratitude	Text, graphics, video	● Write down 3 good things that happened today ● Write down 1 + thing that the participant is grateful for ● Meditation – Breath retraining
Mindfulness and Self-Compassion	Informal mindfulness, self-compassion	Text, graphics, video	● Write down 1 + things that participant wants to be mindful of ● Choose the self-compassionate statement in 4 multiple choice scenarios; practice using self-compassion skills on personal situations ● Meditation – Mindful breathing
Reappraisal and Coping	Learning positive reappraisal and coping skills	Text, graphics, video	● Choose the positive reappraisal statement in 3 multiple choice scenarios; practice using positive reappraisals on personal situations Meditation – Mountain meditation
Values, Strengths, and Goals	Taking inventory of values and strengths; applying values and strengths to setting goals	Text, graphics, video	● Practice on 2 scenarios to set an attainable goal, ordering steps to achieve goal, and attaching values and strengths ● Set own attainable goal, setting steps, and attaching values and strengths, track during check in. ● Meditation- Mindful meditation

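### The undefined predictor *days self-reported ART* probably measures adherence itself, so its association with adherence or viral suppression would not reflect use of the self-monitoring feature

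*Protocol article*

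**What the plan says.** The last paragraph of the statistical text under Aim 1b plans secondary analyses of the association of "individual features of the START intervention (e.g., number of logins, days self-reported ART, number of modules completed) with ART adherence and VL suppression". The three features in brackets are given as examples. On their role in the model it says: "These components of the intervention will be treated as predictor variables in regression models". The models are described as "containing intervention arm as the primary independent variable and adjust for any necessary demographic factors"; baseline adherence is not named.

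The ART feature is not defined. In Table 1 the Check-In is the app element that collects an ART self-report: "Prompts participant to choose current mood, report if they took their HIV medications yet". On frequency of use, the section on the START mHealth application says of participants that "they are asked to engage with the app several times per week for six months".

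The Outcomes section and Table 2 measure adherence with two self-report survey instruments, the Wilson items and a visual analogue scale (VAS), both also collected at the first baseline assessment. Viral load is a laboratory result from the dried blood spot.

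**The concern.** Logins and modules completed describe how much a man used the app. A count of days on which he reported having taken ART also describes how adherent he was. Used as a predictor of survey-reported adherence, it relates two self-reports of the same behaviour. Used as a predictor of suppression, it relates adherence to its expected consequence.

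Either coefficient would tend to be positive whether or not recording doses helps anyone. START joins self-monitoring to positive-affect skills, and an analysis of individual features is informative only if a coefficient says something about engagement with that feature. This one would not. Adjusting for arm and demographics does not remove stable differences in adherence between men, and the overlap remains when only START men are analysed.

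**Working it through.** The plan gives no figure for this analysis, so there is nothing to reproduce. The check has three parts.

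**1. How the count is built, if it means days reported as taken**

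Count = (days with an ART check-in) × (share of those days with ART reported as taken). The first factor is use; the second is reported adherence.

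- Equal use: two men each check in 3 times a week for 26 weeks, so 3 × 26 = 78 days. At 95% adherence the score is 0.95 × 78 = 74; at 60% it is 0.60 × 78 = 47. The whole difference is adherence.
- It is also not a clean adherence score, because days without a check-in add zero. At 3 check-ins a week, a fully adherent man can score at most 78 of 182 days (43%). A man who is 60% adherent and checks in daily scores 0.60 × 182 = 109.

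**2. Size of the built-in association**

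Inputs from the article: up to 250 men (Abstract) and 20% attrition (Statistical analyses), giving 250/2 × 0.80 = 100 START men; the power section gives 175 × 0.80 = 140 per group. The two-sided 0.05 level is borrowed from the planned comparisons. All other inputs are assumptions, because the article gives no distributions.

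Model: true adherence A follows a Beta distribution; check-in days d are drawn independently of A; days reported taken are Binomial(d, A); survey adherence is A plus normal error with SD 10 points, limited to 0-100%. The feature has no effect on A. The test is a Pearson correlation with survey adherence.

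| Setting | Days reported taken: mean r | p<0.05 | Days with any ART check-in: p<0.05 |
|---|---|---|---|
| n=100; mean adherence 75%, SD 15-25 points; 1.5-5 check-ins a week | 0.16 to 0.71 | 35-100% | about 3-6% |
| of which 3 check-ins a week (SD 2), adherence SD 20 points | about 0.34 | 97% | about 5% |
| n=100; A ~ Beta(8,2); mean check-in share 0.3-0.9 | 0.12 to 0.67 | 21-100% | about 4-7% |
| n=140; same as the row above | 0.12 to 0.67 | 28-100% | about 4-5% |

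If only 30-100% of a man's check-ins fall after that day's dose, the range in the first row starts at about 29% instead of 35%. The low ends arise where check-in frequency varies widely between men and dilutes the adherence part of the count.

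**3. What happens if adherent men also use the app more**

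With an assumed correlation of 0.3 between checking in and adherence (Beta(8,2) settings, n=100 and 140), days reported taken are significant in 90-100% of runs. The pure use count is also significant, in 54-79% of runs, with mean r about 0.21. The replacement therefore removes the overlap in construct but not confounding by engagement.

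Only survey adherence was simulated. For viral suppression the argument is qualitative and no figure is offered.

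**The case against.** The strongest reply is that the phrase is an undefined example placed between two use counts, and can equally mean days on which the man used the ART item at all. On that reading there is no overlap. The definition may also be in an analysis plan that is not shown. This stands as a limit: the article does not say that the variable counts days ART was taken. The Check-In prompt makes that the likelier reading, not a certain one.

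Three stronger inferences are tempting, and the documents do not support them.

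- *The outcome is on both sides of the model.* It is not. The Wilson items, the VAS and the blood-spot viral load are not calculated from app logs. The overlap is of construct, not of data.
- *The plan would declare self-monitoring effective.* The text promises an association only, in a secondary analysis, although it does call these variables components of the intervention.
- *The simulated percentages are Type I error rates.* In the simulation the count really is associated with adherence. The percentages show how often a significant association appears when the feature has no effect, which matters only if the coefficient is read as saying something about the feature.

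It is also fair that logins and modules are open to confounding by engagement, so redefining one variable does not make this analysis causal.

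**Conclusion.** The point holds conditionally. If *days self-reported ART* means days on which ART was reported as taken, one of the three named measures of feature use carries the outcome construct, and its association with adherence or suppression cannot be read as reflecting the self-monitoring component. With no feature effect and use unrelated to adherence, a significant association with survey adherence appears in roughly 35-100% of runs at n=100 (from 21% under the other adherence distribution tried), against about 5% for a use count. These ranges rest on assumed distributions of adherence, check-in frequency and survey error.

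If the phrase means days with any ART report, there is no built-in overlap and only the wording needs fixing. On either reading the primary outcome and the comparisons between arms are untouched. The change is worth making because it is almost free and settles the meaning before results are seen.

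**What to change.** In the secondary-analysis paragraph under Aim 1b, replace *days self-reported ART* with: *number of days in months 0-6 with a completed ART check-in, whatever the answer*. Add baseline ART adherence to the adjustment; Table 2 shows that it is already collected at the first baseline assessment.

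If app-reported adherence is of interest, report it descriptively for START men as days reported taken divided by days with an ART check-in, and do not use it as a predictor of adherence or suppression. Continue to present the feature results as associations, since confounding by general engagement remains.

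The cost is a sentence or two of analysis wording. Check-in data are already available in the backend user reports described under the engagement procedures, so no new collection is needed. The downside is that the reported association for this feature will probably be weaker.
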